For concreteness, we consider designing an HIV vaccine efficacy trial among young women (18–35 years old) in southern Africa, where there is one of the highest burdens of HIV globally [1]. The population-based design enrolls young women vulnerable to acquiring HIV in communities with high HIV burden as depicted by antenatal seroprevalence surveys and routine HIV testing services. Women in subpopulations with targeted HIV prevention strategies implemented by their Ministries of Health, e.g., sex workers, are not enrolled. Rather, the design enrolls young women vulnerable to acquiring HIV by virtue of living in areas with high HIV prevalence. Eligibility criteria are as broad as possible, to enhance recruitment and generalizability. At screening, enrollment, and throughout the trial, women are educated about effective prevention of HIV and linked to PrEP and other HIV prevention services in the community; thus, it is important that the trial is conducted in areas in which some form of PrEP is available. These two design elements—recruiting young women from the general population and leveraging the community standard of prevention, defined in partnership with the community—are aspects of the population-based design that differentiate it from a traditional HIV prevention efficacy trial (Table 1). Young women enrolling in the trial are randomized to receive the vaccine or a placebo, where all trial participants have access to community-based HIV prevention modalities (Figure 1). The design answers what is arguably the most critical and community-relevant question around an HIV vaccine: Can the vaccine reduce HIV incidence further, beyond what has been achieved with the currently available HIV prevention package? Blinding of trial participants to the intervention, i.e., the use of a placebo, is critical for reliably evaluating the ability of the vaccine to protect. Prior experience in HIV [54] and other infectious disease trials [55] has demonstrated that knowledge of the intervention received may affect participant behavior and threaten the reliable estimation of vaccine efficacy. Additionally, experience demonstrates that in an open-label trial, participant retention and compliance with study visits and procedures are likely to differ across arms [56], thus affecting the capture of HIV acquisition and safety outcomes.

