To illustrate this concept, suppose, for example, that HIV recency tests are given to all individuals screened for the population-based trial. With the recency testing data, the HIV incidence in the population from which participants are recruited can be estimated [83,84,85]. Consider the population-based design with 10,067 participants to detect 60% vaccine efficacy with 90% power under a 1.5% placebo-group HIV incidence. The power to evaluate VE is 94.5%, exceeding the target of 90% but additionally satisfying the requirement of at least 30 acquisitions in the vaccine group for immune correlates analysis. This design will be underpowered if incidence is in fact 0.75%, i.e., 50% lower than anticipated. Figure 3 demonstrates this by considering the properties of confidence intervals at the end of the trial, whereas power is relevant in advance of the trial. For the 10,067-person trial, the probability that a one-sided 97.5% confidence interval excludes the null of VE = 0% is 71.6% if the placebo-group incidence is 0.75%. In contrast, this probability is 82.1%, 83.8%, or 86.9% if the trial is augmented with HIV recency data for those screened for trial participation, assuming 10%, 8%, or 5% of those screened are positive for HIV and recency test performance as assumed for the Purpose 1 trial in adolescent girls and young women [10] (recent acquisition if the normalized optical density from the Sedia Limiting Antigen Avidity Enzyme Immunoassay (LAg-EIA) is below 1.5 and HIV-1 RNA viral load > 1000 copies/mL; mean duration of recent acquisition = 184 days, relative standard error = 7%; false recency rate = 1.5%, relative standard error = 70%; 70% of those HIV-negative at screening enroll). For comparison, the probability is 82.6% for a much more resource-intensive approach of expanding the trial sample size by one-third, for a total of 13,390 participants. Notably, these calculations assume that the external control provides an unbiased estimate of placebo HIV incidence, and thus its intended use in the population-based design is to enhance secondary, rather than primary, estimates of vaccine efficacy. In summary, augmentation with external control data is a resource-efficient approach to increasing the precision of vaccine efficacy estimation which is especially important if trial incidence is lower than expected.

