Adherence to the vaccine regimen may be a challenge for a bnAb-inducing vaccine regimen that likely requires four or more doses to protect. Large, population-based vaccine trials most often evaluate simpler vaccine regimens, and many take place when there is already evidence of vaccine efficacy based on prior randomized trials. Attention to minimizing the number of vaccine doses will be needed to maximize adherence in the efficacy trial.

Given that the population-based design seeks to enroll young women in the general population, screen-to-enroll rates may differ from those seen in previous HIV prevention trials conducted in high-risk subpopulations. At the same time, adopting community-based recruitment practices used by outreach vaccination campaigns, including through community health clinics, community outreach programs, and using mobile clinics, is expected to increase the reach of recruitment strategies. Employing broad eligibility criteria obviates the need for risk-based screening practices common in traditional HIV prevention trials in high-risk subpopulations, thus enhancing the efficiency of screening. These features of the population-based design support the feasibility of enrolling large numbers of young women in the general population, while enhancing the generalizability of trial results.

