**Figure 3 vaccines-14-00794-f003:**
[figure not shown]
Probability that a one-sided 97.5% confidence interval for VE excludes VE = 0% based on analyses that augment the population-based design with external control data, as a function of the placebo-group HIV incidence. The black curve is the probability for the “baseline” population-based design that enrolls 10,067 participants to detect 60% vaccine efficacy with 90% power under 2:1 randomization and 1.5% placebo incidence. The red curves represent the probability for the baseline design that also applies HIV recency testing to all individuals screened for trial participation, assuming 5%, 8%, or 10% HIV prevalence among screened individuals. The black dashed curve is a reference and shows the probability for a design that is one-third larger than the baseline design: it enrolls 13,390 participants who are randomized 1:1 to vaccine:placebo. All calculations assume a one-year vaccination series, a 15% annual loss to follow-up, and that the primary analysis counts infections 2 weeks post-last-immunization through month 24.

**Table 1 vaccines-14-00794-t001:** Attributes of a population-based HIV vaccine trial in comparison to a traditional HIV vaccine trial.

	Population-Based Design	Traditional Design	Implications for Population-Based Design
Trial population	General population, with broad eligibility criteria in communities with high HIV burden	High-risk subpopulation, e.g., in key population(s) or with multiple behavioral risk factors for HIV	Results of a population-based trial generalize to the general population instead of high-risk subpopulation(s)
Background standard of prevention provided to all trial participants	Referral to community-based HIV prevention services	Trial standard of prevention, i.e., prevention “package” provided that may cover the cost of PrEP or prescribe/deliver PrEP	Vaccine efficacy is interpretable as the percentage reduction in HIV incidence, relative to the community standard of prevention instead of the trial standard of prevention
Participant recruitment centers	Community health clinics, community outreach programs, mobile clinics or social media	Clinical research sites or social media	Recruitment of more diverse and representative participants in the community

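### The recency estimate that augments the placebo arm is taken over everyone screened; limit it to women who meet the entry criteria other than HIV status

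*Protocol article*

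**What the plan says.** Section 4 offers augmentation with external control data as an optional safeguard against low incidence. Its worked illustration supposes that "HIV recency tests are given to all individuals screened for the population-based trial", so that "the HIV incidence in the population from which participants are recruited can be estimated". It also assumes that "70% of those HIV-negative at screening enroll". The Figure 3 legend repeats the sampling frame: the augmented design "also applies HIV recency testing to all individuals screened for trial participation".

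Section 2 sets one named exclusion: "Women in subpopulations with targeted HIV prevention strategies implemented by their Ministries of Health, e.g., sex workers, are not enrolled". Otherwise, "Eligibility criteria are as broad as possible, to enhance recruitment and generalizability". Section 3 gives enrolment of women outside the groups targeted for prevention as one of its two reasons for assuming an incidence below the 3–4% seen in recent trials.

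Section 4 acknowledges that "these calculations assume that the external control provides an unbiased estimate of placebo HIV incidence", and for that reason confines the augmented analysis to secondary use. Nothing in the article limits the recency sample to women who could otherwise have enrolled, or says whether excluded groups are removed before screening.

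**The concern.** The recency estimate is combined with the randomised placebo arm as a second measure of placebo incidence. That is sound only if both describe the same kind of woman. As written, the frame for the first is everyone screened, while the frame for the second leaves out groups that Section 3 implies have higher incidence. If women from those groups reach screening, their recent infections and HIV-negative numbers enter the external control but cannot enter the trial. The external rate would then sit above the trial's true placebo rate, and the augmented efficacy estimate would be too favourable.

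The augmented analysis is meant to support interpretation when the primary result is imprecise because incidence is low. That is also when the external data carry most weight. Section 7 warns that bias in a counterfactual placebo matters much more for a product of modest efficacy.

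**Working it through.** **Inputs from the article.** N = 10,067, 2:1 allocation, VE 60%, placebo incidence 0.75%, 15% annual loss, infections counted from two weeks after the last dose (taken as month 12.5) to month 24, one-sided 0.025. Recency: mean duration 184 days (relative SE 7%), false recency rate 1.5% (relative SE 70%), prevalence 10%, 8% or 5%, and 70% of HIV-negative women screened enrol. **Assumed:** recency cut-off T = 2 years, loss as a rate of 0.15 per year.

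**Trial events.** With hazard h and r = h + 0.15, events per arm = n·(h/r)·[exp(−r·12.5/12) − exp(−2r)]. At 0.75% this gives 15.3 vaccine and 19.0 placebo events at VE 60%, and 38.0 and 19.0 at VE 0%. Schoenfeld power with 34.3 events is 71.6%, as stated.

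**Recency estimate.** HIV-negative screened = 10,067/0.7 = 14,381. The effective recency window is B = 184/365.25 − 0.015 × 2 = 0.474 years. Expected true recent infections are A = 0.0075 × 14,381 × 0.474 = 51.1. The delta-method variance V of log incidence adds sampling error, false-recency error and duration error. At 5% prevalence (757 positive) V = 0.0219 + 0.0014 + 0.0124 + 0.0055 = 0.0412, so 1/V = 24.2.

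**Pooling.** External weight w = (1/V)/(E_p + 1/V), where E_p is the expected number of placebo events. Probability = Φ(−ln 0.4 / √(1/E_v + 1/(E_p + 1/V)) − 1.96), where E_v is the expected number of vaccine-arm events. At 5% prevalence w = 24.2/(19.0 + 24.2) = 0.561, and the probability is Φ(0.916/0.297 − 1.96) = 86.9%.

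| Prevalence | 1/V | Weight w | Reproduced | Stated |
|---|---|---|---|---|
| 10% | 8.7 | 31.5% | 82.1% | 82.1% |
| 8% | 13.0 | 40.6% | 83.8% | 83.8% |
| 5% | 24.2 | 56.1% | 86.9% | 86.9% |

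T = 1 year gives 81.9%, 83.5% and 86.5%. The augmented figures match this Wald form, under which the unaugmented figure is 76.0% rather than 71.6%; that is a separate matter.

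**How large could a mismatch be?** If a share f of those tested could not enter the trial and has k times the incidence, the external-to-trial ratio is 1 − f + f·k. The article gives neither f nor k. As assumptions: f = 5%, k = 3 gives 1.10; f = 10%, k = 3 gives 1.20; f = 30%, k = 2 gives 1.30. The last uses the full 30% who do not enrol, which is the ceiling for f.

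**Effect on an inert vaccine.** Apparent VE = 1 − ratio^(−w). One-sided error = 1 − Φ(1.96 − w·ln(ratio)/SE₀), with SE₀ = √(1/38.0 + 1/(19.0 + 1/V)). At 5% prevalence and ratio 1.30, w·ln 1.30 = 0.147 and SE₀ = 0.222, so VE = 13.7% and error = 1 − Φ(1.298) = 9.7%.

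| Ratio | Apparent VE, fixed weights | One-sided error, fixed weights | Apparent VE, weights reset | Error, weights reset |
|---|---|---|---|---|
| 1.10 | 3.0–5.2% | 3.3–4.3% | 3.3–5.5% | 3.4–4.5% |
| 1.20 | 5.6–9.7% | 4.2–6.7% | 7.0–10.8% | 4.8–7.6% |
| 1.30 | 7.9–13.7% | 5.2–9.7% | 10.7–15.7% | 6.9–12.4% |

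Each range runs from 10% to 5% prevalence. In the last two columns the inflated rate also sets the weights. At k = 1 there is no bias. At f = 30% and k = 0.5 (ratio 0.85, weights reset) it reverses: a true 60% reads 57–58%.

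**Cost of restricting.** Keeping prevalence and incidence unchanged and cutting the recency sample to 90% of its size gives 81.9%, 83.7% and 86.6%. Cutting it to 70% gives 81.6%, 83.2% and 85.8%.

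**The case against.** The passage is an illustration of a feature that could be considered, not an adopted rule, and an article may leave the sampling frame to a full protocol. The authors state the unbiasedness assumption, draw the consequence that the analysis is secondary only, and warn in Section 7 against relying on a counterfactual placebo. All of this stands. It limits the weight of the point, but the all-screened frame is stated twice and generates the published probabilities, and this source of bias is not named.

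A reader might infer that the external control is known to describe a different population and will inflate efficacy. The article does not support that. It says targeted groups are not enrolled; it does not say they are screened. It gives no reason why 30% of HIV-negative women do not enrol, and they may be eligible women who decline. It also says that "Employing broad eligibility criteria obviates the need for risk-based screening practices common in traditional HIV prevention trials", which suggests that few are turned away on risk. Nor does it list what is recorded at screening, so one cannot say that the data needed for a restriction are already planned.

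Finally, women found HIV-positive can never enrol yet must be in a recency sample, so testing some women who do not enter is inherent to the method. That is why the restriction has to be on criteria other than HIV status. It would not remove bias from eligible women who decline.

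**Conclusion.** The point holds as a risk in a secondary, optional analysis. The stated frame is wider than the trial's, and the one named exclusion concerns women whom Section 3 implies have higher incidence. With 31.5% to 56.1% of the control weight on recency data, an assumed 10% to 30% inflation gives an inert vaccine an apparent efficacy of about 3% to 14% and a one-sided error of about 3% to 10%, somewhat more if the inflated rate also sets the weights. These sizes rest on assumed shares and relative incidences, on T = 2 years and on inverse-variance pooling. The direction is likely upward if excluded women are tested, but it is not established. The primary randomised comparison and its 2.5% error rate are untouched. It is worth changing because the better rule is cheap.

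**What to change.** In Section 4 and the Figure 3 legend, define the recency sample for the augmented analysis as screened women who meet the entry criteria other than HIV status. Ask about membership of excluded groups before the HIV result is known, so that HIV-positive and HIV-negative women are classified alike.

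Keep the all-screened estimate as a sensitivity analysis over a range of external-to-trial incidence ratios, including values below 1. State that bias from eligible women who decline remains. Present the 82.1% to 86.9% as conditional on the otherwise-eligible fraction, shown over an assumed range because the article does not give that fraction.

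The cost is the ordering of some screening questions, a recalculation and a smaller recency sample. Even at a 70% fraction, with prevalence and incidence unchanged, the probabilities fall by only about 0.4 to 1.1 percentage points.

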## 5. Optimizing Compliance and Recruitment

Decentralization, e.g., using mobile vans, buses, and temporary “pop-up” clinics to deliver the vaccine, is a key attribute of the population-based design (Table 1). Widely implemented for routine immunization programs and supplementary immunization activities in low-resource and geographically dispersed settings, decentralized approaches have consistently demonstrated their value in reaching populations that are otherwise missed by facility-based services, including rural communities, informal urban settlements, mobile populations, and individuals facing structural barriers such as transport costs or time constraints [86,87]. Applying these strategies to an HIV vaccine efficacy trial is anticipated to substantially reduce participant burden by bringing trial services closer to where people live and work, thereby improving recruitment and enhancing the representativeness of the study population. Importantly, these approaches can also foster community trust and engagement when implemented in partnership with local leaders and health workers, and trust is especially critical for an HIV vaccine trial where stigma and hesitancy may affect trial participation.

Experience from outreach vaccination campaigns also highlights the operational feasibility of delivering complex interventions outside traditional clinical settings, provided that systems are carefully designed [88,89]. Mobile teams have successfully administered vaccines, conducted screening, and collected biological specimens in field conditions, often supported by standardized protocols, task-shifting to trained mid-level providers, and strong supervisory structures. For the population-based HIV vaccine trial, this could suggest a hybrid model wherein initial screening and consent are conducted at the community level, with mobile units facilitating follow-up visits, specimen collection, and data collection and adverse event monitoring. Digital tools—such as electronic data capture, real-time monitoring dashboards, and mobile communication platforms—can further strengthen decentralization by enabling timely data transmission, participant tracking, and adaptive management of field operations. Self-collection of HIV status using self-testing or self-collection of blood (e.g., using the Tasso devices) that are mailed and tested in a central lab may provide additional resolution on the timing of HIV acquisition, which is important for immune correlates analyses. Central lab testing is preferred for vaccines that may cause vaccine-induced seroreactivity (VISR)- a determination that will be made in prior phase 1 and 2 studies of the vaccine; the central laboratory will use a specialized diagnostic algorithm to differentiate HIV infection from VISR. While VISR rates have been low in recent phase 1 trials of candidate bnAb-inducing vaccines ([name], personal communication, 26 August 2026), VISR likely needs to be entirely ruled out in order for home testing to be employed. The HIV diagnostic algorithm that is employed will also need evaluation in the context of the evolving state of knowledge around accurate HIV infection diagnosis in the context of long-acting injectable PrEP [90].

However, decentralization introduces important risks that must be proactively mitigated. Maintaining cold-chain integrity for investigational products is more complex in mobile settings and requires robust solutions, including validated portable cold-chain equipment, continuous temperature monitoring devices, and contingency plans for equipment failure. Similarly, ensuring data quality and protocol adherence across dispersed sites necessitates rigorous standard operating procedures, comprehensive staff training, and frequent quality assurance checks, potentially supported by remote monitoring technologies. Another consideration is the standard practice for HIV prevention trials to provide comprehensive sexual health care to trial participants—including contraceptive counseling and screening for STIs. Mobile services could be designed to incorporate these services as well. Participant retention, often a challenge in decentralized trials [91,92], can be addressed through strategies proven in immunization programs, such as appointment reminders, community-based follow-up, and flexible scheduling aligned with participants’ daily routines. The population-based design may also have lower compliance with study procedures than a trial conducted in a high-incidence subpopulation due to competing life challenges. The sample size calculations above anticipate this: a substantially lower rate of retention is used than that seen in recent HIV prevention efficacy trials among young women in southern Africa. Secondary analyses must be prospectively planned to address potential bias caused by lower retention rates for specific populations (i.e., informative censoring) and to evaluate vaccine efficacy in a hypothetical world in which all individuals receive the full vaccination series. Overall, while mobile and outreach approaches introduce logistical complexity, the experience from immunization programs suggests that, when well-executed, they can substantially enhance equity, feasibility, and external validity in large-scale vaccine trials [69,86,92].

Adherence to the vaccine regimen may be a challenge for a bnAb-inducing vaccine regimen that likely requires four or more doses to protect. Large, population-based vaccine trials most often evaluate simpler vaccine regimens, and many take place when there is already evidence of vaccine efficacy based on prior randomized trials. Attention to minimizing the number of vaccine doses will be needed to maximize adherence in the efficacy trial.

Given that the population-based design seeks to enroll young women in the general population, screen-to-enroll rates may differ from those seen in previous HIV prevention trials conducted in high-risk subpopulations. At the same time, adopting community-based recruitment practices used by outreach vaccination campaigns, including through community health clinics, community outreach programs, and using mobile clinics, is expected to increase the reach of recruitment strategies. Employing broad eligibility criteria obviates the need for risk-based screening practices common in traditional HIV prevention trials in high-risk subpopulations, thus enhancing the efficiency of screening. These features of the population-based design support the feasibility of enrolling large numbers of young women in the general population, while enhancing the generalizability of trial results.

